### Participants

Subjects will be 60 premenopausal obese women aged 18 years or more. The following inclusion criteria will be applied: aged 18 years and older, BMI range of 30 to 40 kg/m^2^, absence of menopause, lactation, pregnancy and food allergies, not having cancer, hepatic, renal, thyroid and gastrointestinal disorders, no surgery for weight loss, no weight loss over the past 6 months, no taking herbs and drug that reduce appetite and weight and vitamin-mineral supplements. The participants with any of the following criteria will be excluded: become pregnant during study, unwilling to continue. At the end of the intervention, if the remained powders exceed 10% of total administered powders, that subject will be excluded from the study.

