## Methods

### Design

We will carry out a 2 months’ open label, parallel-group, randomized controlled trial. The proposed clinical trial will be held at the Nutritional research center, department of Nutrition, Ahvaz Jundishapur University of Medical Science for 2 months to assess the efficacy of daily whey 30 mg supplementation in obese subjects Figs. 1 and 2.

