### Sample size

The sample size was calculated according to the changes in anandamide level, in response to weight loss, based on the study conducted by Mallipedhi et al. [16]. It was calculated considering 95% confidence interval, 80% power (α = 0.05 and β = 0.2), and the related mean and SD of anandamide levels in the mentioned study (μ1 = 0.297; μ2 = 0.209; SD1 = 0.042; SD2 = 0.049). Finally, 30 subjects were recruited for each group.

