### Measurements

A questionnaire about patients’ demographic situations, diseases, and medications, diabetes history and probable supplementations will be recorded at the beginning of the study. Dietary intake will be assessed by 3 days 24-h recall questionnaires (2 week days and 1 weekend day) at the baseline, middle and the end of study. Total energy and macronutrients intake will be calculated by using Nut IV (the Hearst Corporation, San Bruno, CA). To assess physical activity levels the International Physical Activity Questionnaire (IPAQ) will be used at the baseline and the end of study. Anthropometric parameters will be measured after overnight fasting with minimal clothing and without shoes. In all visits (every 15 days), body weight will be measured with the accuracy of 100 g using seca scale. Stature will be measured in a relaxed position using seca stadiometer with accuracy of 0.5 cm. BMI will be calculated as body weight (kg) divided by the square of height(m). Waist circumference will be assessed at above the iliac crest, just below the lowest rib margin at the end normal expiration to the nearest 0.5 cm. TANITA BC-418 body composition analyzer will be used to calculate total body fat and fat percent, fat free mass and fat free mass percent.

At baseline and end of the trial, 10 ml of venous blood samples (2 ml in EDTA- coated sterile tubes and 8 ml in regular tubes) will be collected after 10–12 h overnight fasting. For determination of plasma AEA and 2-AG, the blood in EDTA coated tubes will be centrifuged at 1500 g at 4 °C for 15 min and will be stored at -80 °C. These variables will be quantified by liquid chromatography/in-line mass spectrometry [7]. Regular tubes will be used for biochemical analyses such as determination of glucose, insulin, total cholesterol, HDL-C, triglyceride, adiponectin, leptin, TNF-α and IL-6 in serum. Blood glucose and lipid profile will be determined by enzymatic method with kits from Pars-azmoon (Tehran, Iran). LDL-C levels will be calculated by the Friedewald equation. Circulating insulin will be measured by immunoassay. Homeostasis model assessment – insulin resistance(HOMA-IR) will be calculated by the following formula: fasting glucose(mg/dl) × fasting insulin(μu/ml)/405. ELISA kits will be used to measure serum adiponectin and leptin levels.

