### Analysis

SPSS version 17 (SPSS Inc., Chicago, IL, USA) will be used for data analysis. All data will be presented as mean ± SD. The percent change of each variable will be also calculated by the formula [(E − B)/B × 100], where E is the end of treatment values and B is the baseline values. The normality of variables will be tested using Kolmogorov- Smirnov test. Independent sample t-test and the paired sample t-test will be applied for comparing parametric continuous data between and within the groups, respectively. Mann-Whitney test and Wilcoxon test will be used to test the differences in asymmetric variables between and within the groups, respectively. To control confounding variables, analysis of covariance (ANCOVA) test were used to determine the differences between the two groups post-intervention, while adjusting for baseline measurements and covariates. A *p* value less than 0.05 will be considered to be statistically significant.

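### Excluding women in either arm who are unwilling to continue, without separating stopping the intervention from withdrawing consent, forfeits their 2-month blood outcomes and can bias an open-label comparison

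*Protocol article*

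**What the plan says.** After the inclusion criteria, the Participants section of the protocol article gives a rule for women already in the trial: "The participants with any of the following criteria will be excluded: become pregnant during study, unwilling to continue". The reference to pregnancy arising during the study, and the idea of continuing, place the rule after enrolment. It is not limited to one arm. The next sentence adds a powder-return rule: "if the remained powders exceed 10% of total administered powders, that subject will be excluded from the study".

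The Measurements section sets the blood schedule: "At baseline and end of the trial, 10 ml of venous blood samples". These samples supply anandamide (AEA), 2-AG, glucose, insulin, lipids, adiponectin, leptin, TNF-α and IL-6. The one outcome stated for interim visits is weight: "In all visits (every 15 days), body weight will be measured with the accuracy of 100 g using seca scale".

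The Design section states: "We will carry out a 2 months’ open label, parallel-group, randomized controlled trial". The Analysis section compares the groups by t-test or Mann-Whitney test and by ANCOVA on post-intervention values adjusted for baseline. It also computes percent change from baseline. Each of the post-intervention comparisons needs an end value.

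**The concern.** Two different events are merged under one phrase. A woman may stop the diet or the powder and still be willing to give a final blood sample, or she may withdraw consent to any further measurement. Only in the second case must data collection end. As written, both lead to exclusion.

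The blood outcomes have no interim value, so a woman excluded before the end has nothing to analyse beyond baseline. An analysis plan can decide how to handle a missing value, but it cannot recover a sample that was never drawn.

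What remains is a comparison of women who stayed. Both arms know their allocation, only one receives a daily product, and both follow an energy deficit of at least 800 kcal. Willingness to continue could therefore depend on the arm and on perceived progress. If it does, the retained groups are no longer the randomised groups, and a whey effect could be created or hidden. The article does not show that this will happen, but its rule removes the data that would guard against it.

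**Working it through.** **1. What the text fixes, side by side**

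- Participants: women in either arm who are unwilling to continue are excluded.
- Measurements: blood is taken at baseline and at the end of the trial only.
- Analysis: the outcome comparisons need an end value.
- Nothing in the article provides for an end measurement after stopping, and nothing reverses the exclusion.

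Together these give no 2-month blood outcome for an excluded woman. This is an inference from the exclusion and the schedule; the article does not say it in those words.

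**2. The plan's own figure**

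The only related figure is the sample size of 30 per arm. Its inputs are "μ1 = 0.297; μ2 = 0.209; SD1 = 0.042; SD2 = 0.049", with α = 0.05 and 80% power.

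- Pooled SD = √((0.042² + 0.049²)/2) = 0.0456
- Difference = 0.297 − 0.209 = 0.088, so d = 0.088/0.0456 = 1.93
- n per arm = 2 × (1.96 + 0.84)²/1.93² ≈ 4.2, rounded up to 5

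The inputs do not reproduce 30. That is a separate matter, and the present point does not depend on it. The sample size section states no stopping rate, so none can be taken from it.

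**3. A simple model for the bias**

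Let p be the proportion who stop in an arm, and let stoppers do worse than completers by D, in SD units, with the same D in both arms. If c is the completer mean and m the mean of all randomised women:

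m = (1 − p) × c + p × (c − D) = c − pD, so c = m + pD.

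The completer contrast therefore differs from the all-randomised contrast by (p in whey − p in control) × D.

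Assume no true effect, 30 randomised per arm, and these stopping rates (assumptions, not from the document). The type I error is for a two-sided 5% test, by normal approximation.

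| Stopping, control vs whey | D = 0.5 | D = 1.0 |
|---|---|---|
| 10% vs 10% | 0 (5.0%) | 0 (5.0%) |
| 10% vs 20% | 0.05 SD (5.4%) | 0.10 SD (6.5%) |
| 10% vs 30% | 0.10 SD (6.4%) | 0.20 SD (10.6%) |

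One cell in full: for 10% vs 30% with D = 1.0, the bias is 0.20 × 1.0 = 0.20. With 27 and 21 women left, SE = √(1/27 + 1/21) = 0.291 and 0.20/0.291 = 0.687. Then Φ(0.687 − 1.96) + Φ(−0.687 − 1.96) ≈ 0.102 + 0.004 = 0.106.

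The labels can be swapped: more stopping in the control arm gives the same size with the opposite sign.

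**4. Loss of precision**

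With 30 per arm, the difference detectable with 80% power is (1.96 + 0.84) × √(2/30) = 0.72 SD. If 10%, 20%, 30% or 40% of each arm is lost (27, 24, 21 or 18 left), power for that difference falls to 76%, 71%, 65% or 58%. For the plan's own d = 1.93 it stays above 99.9%. On the plan's own assumptions, then, the issue is bias and not power.

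**The case against.** **The phrase may mean withdrawal from the trial.** It has no object and names neither diet nor powder. It stands beside pregnancy, and incomplete powder use has its own rule in the next sentence. If every such woman withdraws consent, changing the words recovers little. This stands as a limit, and it means that one cannot say the article equates stopping the diet with leaving the study. The wording covers both cases, and women who have merely stopped would be lost needlessly.

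**Analysis sets and missing data belong to documents not shown.** This also stands, so the absence of an analysis-set definition is not part of the point. The exclusion rule is different because the article states it, and its effect falls on data collection.

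**Retention measures exist.** Contact every three days and powder supply every 15 days may keep stopping low. They do not change what happens to a woman who stops.

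Three stronger readings are tempting but not supported:

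- *Two end dates.* The Analysis section defines its follow-up value thus: "where E is the end of treatment values and B is the baseline values". A reader might infer that women who stop early are sampled early. Treatment and trial share the same fixed 2 months, and the phrase only defines a percent-change formula. It sets no visit.
- *Body composition is lost in the same way.* The article gives no timing for the waist and body-composition measurements, and weight is taken every 15 days. Only the blood outcomes are clearly limited to two time points.
- *A bias of 0.19 or 0.39 SD.* A reader might combine the 0.088 anandamide difference with zero change in every stopper: 0.088 × 0.10 = 0.0088 (0.19 SD) and 0.088 × 0.20 = 0.0176 (0.39 SD). The arithmetic is right, but it sets a gap of 1.93 SD between completers and stoppers, which nothing in the document supports. Completers in both arms would also change equally, so the example does not show exclusion creating a whey effect.

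**Conclusion.** The point holds in a limited form. The article excludes women who are unwilling to continue, in both arms, without distinguishing stopping the intervention from withdrawing consent to measurement. With blood drawn only at baseline and the end, those women have no follow-up value for the endocannabinoid and biochemical outcomes, and the open-label comparison rests on women who stayed.

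The size of any bias is unknown. The range of 0.05 to 0.20 SD depends on an assumed 10- to 20-point difference in stopping, on stoppers doing 0.5 to 1.0 SD worse, and on that gap being equal in both arms. Equal stopping gives zero under this model. The document supports neither equal nor unequal stopping.

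This is a cheap and worthwhile correction to make while the trial is still recruiting. It does not show that the trial's result will be wrong. It is also distinct from the powder-return rule, which can act only in the whey arm.

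**What to change.** - Remove unwillingness to continue as a reason for exclusion in the Participants section.
- Distinguish (a) stopping the diet or powder from (b) withdrawing consent for further measurement.
- Invite every woman under (a), in both arms, to the scheduled 2-month visit for the planned fasting blood sample and measurements, and analyse her in her randomised arm.
- Record the date and reason for stopping, by arm, so that differential stopping can be seen and reported.

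The pregnancy criterion and the conduct of the intervention are not touched.

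The cost is amendment wording and the recall of a few women to a visit, with assays, that is already planned. The estimated effect may be somewhat diluted by women who stopped, and some will still decline the visit, so the missing data will shrink but not vanish.

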### Intervention

All participants will follow a hypocaloric diet of 800 kcal below estimated energy requirements, energy needs is estimated by Mifflin Jeor St equation. Control group will follow a hypocaloric diet of 800 kcal below estimated energy requirements and intervention group will follow a hypocaloric diet of 916 kcal below estimated energy requirements, each of intervention group subjects will receive 30-g whey protein powders daily. The powders will be provided in a sachet form (each sachet containing 30-g whey protein). Each 30 g of the whey protein supplement will be contained 116 kcal, 0.5 g of lipid, 0.4 g of carbohydrate, and 27.5 g of protein. Participants will be instructed to add one sachet to 250 ml cold water and consume immediately, every evening. In control and intervention group the macronutrients percent will be carbohydrate 55%, fat 30% and protein15%. Subjects will be asked to record powder intake and to check compliance, they will be followed by the dietitian via phone calls or SMS, every three days and, powders will be given to the subjects every 15 days. To create a variety in the diet while maintaining the general principles of diet, the same dietitian will give a dietary exchange list and a diet according to their food habits. A trained dietitian will design the energy requirements and macronutrient distribution and the same dietitian will be available to train participants on the diet.

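### The 10% leftover-powder rule excludes women after randomisation from the whey arm only, which breaks the randomised comparison and probably biases it towards whey

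*Protocol article*

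**What the plan says.** The Participants section of the protocol article lists grounds for removal after enrolment. Two can arise in either arm: "become pregnant during study, unwilling to continue". A third is judged when the intervention ends: "if the remained powders exceed 10% of total administered powders, that subject will be excluded from the study".

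The Intervention section shows whom the third rule can reach. On the whey side, "each of intervention group subjects will receive 30-g whey protein powders daily". On the other side, "Control group will follow a hypocaloric diet of 800 kcal below estimated energy requirements"; no placebo or comparison powder is described, and no level of diet adherence leads to a control being removed. The Design section calls the study an "open label, parallel-group, randomized controlled trial".

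The Analysis section compares the two groups by t-test or Mann-Whitney test, and by ANCOVA adjusted for baseline values and covariates. It says nothing that would bring back a woman removed under the powder rule.

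**The concern.** Randomisation makes the two groups comparable only if membership of the compared groups does not depend on what happens after allocation. Here it does, and on one side only. A woman in the whey arm who leaves more than a tenth of her sachets is dropped. A woman in the control arm who follows her diet just as poorly stays in. What is compared is adherent whey users against all remaining controls.

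This is not a detail left to a later document. The protocol states the rule, and its wording removes the woman from the study, not from a secondary analysis set. Because it applies once the intervention is over, it does not govern treatment; its effect is to decide who is counted. Baseline adjustment does not repair this, because the selection is on behaviour after baseline.

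At stake is the main between-group comparison for every outcome in the primary aim, including body composition, where diet adherence plausibly matters most.

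**Working it through.** **Inputs from the protocol article**
- Threshold: more than 10% of powder left (Participants).
- One 30 g sachet each evening for 2 months (Intervention, Design). Taking 2 months as 60 days, 10% × 60 = 6 sachets, so 7 or more returned triggers exclusion.
- 30 women per arm; alpha 0.05 (Sample size). Two-sided testing is assumed, as sidedness is not stated.

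**The plan's own figure.** The plan's only related figure is 30 per arm. The stated means and SDs do not reproduce it: difference 0.297 − 0.209 = 0.088, pooled SD √[(0.042² + 0.049²)/2] = 0.0456, and n = 2 × (1.96 + 0.84)² × 0.0456² / 0.088² ≈ 4.2, that is 5 per group. That is a separate matter. The check below takes 30 per arm as given and does not rest on how it was reached.

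**Assumptions, since the protocol gives no figures**
- True effect of whey: zero.
- Fraction q of the whey arm excluded, always the least adherent: 10%, 20%, 30%.
- Correlation r between powder adherence and improvement: 0.3 and 0.5, with 0 and −0.3 to test the sign.

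**Formulas.** Dropping the lowest fraction q on a normal adherence scale shifts the mean outcome of those kept by

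bias = r × φ(z_q) / (1 − q), in SD units.

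The multipliers φ(z_q)/(1 − q) are 0.1755/0.9 = 0.195, 0.2800/0.8 = 0.350 and 0.3477/0.7 = 0.497.

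The standard error is SE = √[1/(30(1 − q)) + 1/30], which is 0.265, 0.274 and 0.285 for 27, 24 and 21 women kept. With s = bias/SE, the two-sided rejection rate is P(Z > 1.96 − s) + P(Z < −1.96 − s).

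Worked case, q = 20%, r = 0.5: bias = 0.350 × 0.5 = 0.175; s = 0.175/0.274 = 0.639; rejection = P(Z > 1.321) + P(Z < −2.599) ≈ 9.8%.

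| Whey arm excluded | r | Spurious difference (SD) | Type I error, formula | Type I error, simulation |
|---|---|---|---|---|
| 10% | 0.3 | 0.058 | 5.6% | 5.7% |
| 10% | 0.5 | 0.097 | 6.6% | 6.6% |
| 20% | 0.3 | 0.105 | 6.7% | 7.0% |
| 20% | 0.5 | 0.175 | 9.8% | 10.3% |
| 30% | 0.3 | 0.149 | 8.2% | 7.8% |
| 30% | 0.5 | 0.248 | 14.1% | 14.1% |

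The simulation used 20,000 trials per row with t-tests on 30 controls against the women kept.

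**Sign.** At r = 0 the bias is zero and the error rate stays near 5%. At r = −0.3 the bias has the same size as at r = 0.3 but runs against whey. With all 30 against 30 kept, the bias is zero and the error rate 5%.

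**Power.** The difference detectable with 80% power is (1.96 + 0.84) × SE: 0.72 SD with 30 against 30, and 0.74, 0.77 and 0.80 SD with 27, 24 and 21 women left in the whey arm.

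**The case against.** The best defence is that the harm depends on quantities the document does not give. The protocol describes contact every three days and dispensing every 15 days, which should keep returns low. At 10% excluded, the inflation is modest (5.7%–6.6% in simulation), and it vanishes if adherence and improvement are unrelated. That stands as a limit on size and direction. It does not defend the rule, which is one-sided by construction and brings no benefit that a secondary analysis would not give.

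A reader might infer several stronger points that the text does not support:

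- **That the bias certainly favours whey.** This needs a positive correlation that no section reports. It is the likely direction, not a demonstrated one.
- **That women are removed after their outcomes are known.** Weight is taken every 15 days and is visible. But the threshold is fixed in advance and rests on a powder count, and plasma for the endocannabinoids is frozen for later measurement. Nothing says those results are known when sachets are counted.
- **That the protocol treats weight loss as the established driver of endocannabinoid change.** The sample size does rest on anandamide change with weight loss, but the Background calls the link with body composition still uncharacterised, and the Aims make it a secondary question. The link is plausible, not settled.
- **That the lost numbers matter in themselves.** Moving the detectable difference from 0.72 to 0.77 SD at 20% excluded is minor.
- **That removing unwilling women is part of the same fault.** That ground can apply in both arms, and how such women are analysed may be set out in an analysis plan that is not shown.

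**Conclusion.** The point holds. A stated rule removes women after randomisation, on post-baseline behaviour, from the only arm that receives powder, and nothing in the document offsets it. It should be corrected before the main comparison is made.

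The bias is probably towards whey. Under the assumptions shown (no true effect, correlation 0.3–0.5, least adherent women dropped), it runs from about 0.06 SD with 10% of the whey arm excluded to about 0.25 SD with 30%, and the nominal 5% error rate becomes about 6% to 14%. The upper end is roughly a third of the 0.72 SD that 30 per arm can detect (0.25/0.72 = 0.35). The harm is bias, not lost power. The one-arm exclusion is a fact of the text; its direction and size are inferences.

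**What to change.** Delete the 10% rule as a ground for exclusion from the study. Seek the final measurements and blood draw from every randomised woman regardless of powder returned, and make analysis in the assigned arm the main analysis.

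Keep the 10% threshold only to define a labelled secondary per-protocol analysis. Defined by powder alone, that set repeats the one-arm selection, so it should ideally carry a comparable diet-adherence criterion in both arms; the dietary recalls at baseline, middle and end are already planned and could supply one.

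The weights taken every 15 days can support a mixed model, so that women who leave early still contribute to weight and BMI. This does not help the blood markers, which are drawn only at baseline and end and so depend on the final visit.

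Rules for stopping the intervention need not change. Women who become pregnant are a separate case, because their final weight and body composition cannot be read in the same way; this point does not turn on them.

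The article reports that the trial is recruiting, so the cost is a change of wording, a matching registry update, some effort to bring back women who used little powder, and some dilution of the estimated effect by non-adherence.

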### Ethics and trial registration

The patients who meet the inclusion criteria will be fully informed about the study’s protocol. This protocol, approved by Medical Ethics Committee of Ahvaz University of Medical Sciences, is in accordance with the Declaration of Helsinki (approval number: IR.AJUMS.REC.1395.729). Each subject will sign an informed consent form. This investigation was registered on Iranian Registry of Clinical Trials (Irct registration number: IRCT2017021410181N8).

